## Abstract

**Background:**

Insomnia is one of the most prevalent sleep disorders characterized by an inability to fall or stay asleep. Available treatments include pharmacotherapy and cognitive behavioural therapy for insomnia (CBTi). Although CBTi is the first-line treatment, it has limited availability. Therapist-guided electronic delivery of CBT for insomnia (e-CBTi) offers scalable solutions to enhance access to CBTi. While e-CBTi produces comparable outcomes to in-person CBTi, there is a lack of comparison to active pharmacotherapies. Therefore, direct comparisons between e-CBTi and trazodone, one of the most frequently prescribed medications for insomnia, is essential in establishing the effectiveness of this novel digital therapy in the health care system.

**Objective:**

The aim of this study is to compare the effectiveness of a therapist-guided electronically-delivered cognitive behavioural therapy (e-CBTi) program to trazodone in patients with insomnia.

**Methods:**

Patients (n = 60) will be randomly assigned to two groups: treatment as usual (TAU) + trazodone and TAU + e-CBTi for seven weeks. Each weekly sleep module will be delivered through the Online Psychotherapy Tool (OPTT), a secure, online mental health care delivery platform. Changes in insomnia symptoms will be evaluated throughout the study using clinically validated symptomatology questionnaires, Fitbits, and other behavioural variables.

**Results:**

Participant recruitment began in November 2021. To date, 18 participants have been recruited. Data collection is expected to conclude by December 2022 and analyses are expected to be completed by January 2023.

**Conclusions:**

This comparative study will improve our understanding of the efficacy of therapist-guided e-CBTi in managing insomnia. These findings can be used to develop more accessible and effective treatment options and influence clinical practices for insomnia to further expand mental health care capacity in this population.

**Trial registration:**

ClinicalTrials.gov (NCT05125146).

## Introduction

Insomnia is a common sleep disorder characterized by difficulties with sleep initiation, consolidation, duration, quality, and maintenance [1]. As a result, insomnia can have deleterious impacts on health, leading to increased risk of mental illnesses, accidents, poor physical health, and shortened life expectancy [1,2]. The disorder is prevalent in 10–30% of the population, particularly common in older adults, females, and individuals with physical and mental comorbidities [3].

Various biological, cognitive, and behavioural mechanisms that regulate sleep can contribute to insomnia. For example, the disorder is associated with physiological hyperarousal, including hypothalamic-pituitary-adrenal (HPA) axis hyperactivity [1,4]. Moreover, cognitive-emotional hyperarousal and sleep misperceptions may also contribute to insomnia [1,4]. Thus, pharmacotherapy that decreases physiologic arousal and cognitive behavioural therapy for insomnia (CBTi) that alters psychological arousal have been the most supported therapeutic approaches for managing insomnia [5,6].

Pharmacotherapy is frequently used to treat insomnia [6]. Benzodiazepine and nonbenzodiazepine drugs such as zopiclone are clinically effective in treating insomnia [5]. However, dependence, tolerance, abuse potential, and adverse effects (e.g., memory impairment, irritability, and confusion) are commonly reported side effects [7,8]. Since insomnia is associated with HPA axis activation, trazodone, the most commonly prescribed sleep aid, aims to counter this effect [7,9]. In a sample of 781 790 adults diagnosed with insomnia, 14.46% of adults used trazodone (95% CI, 14.38%-14.54%) [10]. This antidepressant is often prescribed at doses ranging between 25mg-100mg—lower than what is required for the treatment of depression to achieve sedative and hypnotic effects [7,9]. The prescribed doses reduce the occurrence of tolerance and drug dependency, providing clinical benefits with fewer side effects than benzodiazepine and nonbenzodiazepine drugs [9]. A systematic review of 45 studies provided adequate evidence supporting low-dose trazodone’s safety and efficacy in increasing sleep duration, improving patient-related sleep quality, and decreasing sleep latency when compared to a placebo [11]. However, medication non-adherence and patient preference to avoid pharmaceutical treatment are common challenges in treating psychiatric disorders, like insomnia [12,13]. Uptake of psychotropic medication can be limited due to treatment complexity, stigma, drug-drug interactions, lack of professional support, and medication costs [12]. Furthermore, evidence indicates that for the treatment of psychiatric disorders, patients yielded a significant three-fold preference for psychological treatment relative to pharmaceutical treatment [13]. As a result, the sustainability of pharmaceutical interventions for insomnia is questionable.

An alternative treatment approach is CBTi. Considered the first-line treatment for people with insomnia, CBT is typically delivered in-person, individually or in a group by a trained clinician [14]. CBTi aims to help patients recognize thoughts and behaviours associated with poor sleep and equip them with tools to change their maladaptive cognitive-behavioural patterns [15]. Core components of CBTi include cognitive therapy, stimulus control, sleep restriction, sleep hygiene, and relaxation training [15]. By encouraging patients to use skills and strategies to continually manage their sleep [16], CBT effectively improves insomnia severity, sleep quality, total sleep time, and other sleep-related parameters compared to waitlist control, placebo, or pharmaceutical interventions [17–19]. Additionally, there are fewer side effects, more durable sleep improvements, and fewer relapse episodes than most sleep medications, making it a more optimal treatment option for insomnia [15,20]. While CBTi is efficacious in many patients, several challenges remain in the dissemination of CBTi, including high costs, limited therapist availability, and inadequate accessibility to treatment [21]. Therefore, reducing barriers while maintaining high-quality care is imperative to improving the access and adherence to CBTi.

To address the limitations of in-person care, electronically delivered CBT (e-CBT) emerged as an alternative psychological approach to managing mental illnesses [22]. E-CBT typically consists of 8 to 12 patient-guided and goal-oriented pre-designed sessions [23] that are delivered via telephone, mobile applications, or the web [22]. Here, patients can access psychoeducational materials, practice CBT exercises, and complete worksheets relevant to their mental health challenges through therapist-guided or self-directed formats [22]. Therapist guidance can occur through synchronous (e.g., telephone, videoconferencing) or asynchronous (e.g., secured email, web-based platform communications) interactions. Moreover, e-CBT offers several advantages that can overcome the limitations of in-person CBT, including a low access threshold, reduced costs, and high scalability [24 Wilhelm]. Much of these advantages are a result of patient-therapist time being only a fraction of what is required by traditional in-person methods [24,25]. Since the content and delivery of e-CBT can be easily adapted for the condition being treated, it has shown significant progress in effectively managing various psychiatric disorders, including insomnia [26–28].

E-CBT for insomnia (E-CBTi) could play a key role in enhancing the dissemination of CBTi and improving the accessibility to care. Current literature has highlighted the superiority of e-CBTi to waitlist control, demonstrating significant improvements in total sleep time, sleep quality, and greater reductions in insomnia severity [28]. Furthermore, evidence has shown e-CBTi to have equivalent efficacy to in-person CBTi with no statistically significant differences between sleep efficiency, total sleep time and insomnia severity [29]. While e-CBTi can be an effective and more accessible treatment option for managing insomnia, its mode of delivery has mainly been through self-directed formats without therapist guidance or coaching [22,29]. Self-directed e-CBTi programs (e.g. Sleepio, SHUTi, NightOwl) can be beneficial [22]. However, therapist guidance via synchronous or asynchronous communications and personalized feedback in e-CBT may further improve patient adherence and promote desired treatment outcomes [22,30,31]. At the same time, synchronous therapy programs can be time-consuming, costly and may not be accessible to many patients. Asynchronous online communications, which do not rely on the simultaneous presence of therapists and patients, could be a viable alternative to lower therapy costs, increase care capacity, and improve adherence to e-CBTi [32]. For instance, the “I-Sleep’’ program that delivers e-CBTi along with asynchronous email interactions demonstrated more significant improvements in sleep quality and efficiency than waitlist control [33,34]. Since email communications are riddled with privacy concerns, potential confidentiality breaches, and lack of personalized care, a safe and secured clinic-like web-based interface such as the Online Psychotherapy Tool (OPTT; OPTT Inc.) might be a scalable solution [35–37]. Asynchronous communication with therapists through this platform may provide a safer and more cost-effective opportunity to increase engagement and adherence with e-CBTi.

To the best of our knowledge, studies that examine the effectiveness of asynchronous therapist-guided e-CBTi are limited. While it is known that e-CBTi produces better results compared to waitlist control groups and is comparable to in-person CBTi, its direct comparative effectiveness to active pharmaceutical interventions has not been established [29]. Trazodone is chosen as the representative for pharmacotherapy in this study because of its low abuse potential, high efficacy, and common usage in general practice [7,9,11]. Direct comparisons between trazodone and the scalable therapist-guided e-CBTi in clinical populations would be an important step in benchmarking the effectiveness and utility of this digital therapy in healthcare. The findings of this study will demonstrate the possibility of a novel alternative for treatment of insomnia. The suggested method could be more accessible, available and affordable than in-person CBTi while producing more significant long-term beneficial effects than trazodone in managing insomnia.

### Objective

The primary objective of the current study is to evaluate the comparative effectiveness of therapist-guided e-CBTi to the pharmaceutical drug, trazodone in managing insomnia. It is hypothesized that therapist-guided e-CBTi with personalized feedback will lead to more significant improvement in sleep outcomes when compared to trazodone. The treatment effect of therapist-guided e-CBTi and trazodone on insomnia severity and sleep will be evaluated using online questionnaires, sleep diaries, wearable sensors (Fitbit), and other behavioural variables.

## Materials and methods

### Study design and setting

This study will use a randomized controlled trial design with two parallel arms to compare therapist-guided e-CBTi and trazodone’s treatment effects on sleep outcomes in patients with insomnia. The nature of the comparative effectiveness study will facilitate the investigation of the interventions’ effects under the circumstances that are comparable with clinical settings, which may provide important insights on the interventions’ impacts when integrated into routine clinical practices in the future. In addition, the SPIRIT guideline that outlines the standard evidence-based protocol items in intervention trials has been followed. Fig 1 outlines the schedule for enrollment, intervention, and assessments. This study is a single-site study, and it will run through the Queen’s University Online Psychotherapy Lab (QUOPL), Kingston, Canada. See Fig 2 for the participant flow chart. Ethical approval was received from the Queen’s University Health Science and Affiliated Teaching Hospitals Research Ethics Board (HSREB File #: 6032770). The study is registered with ClinicalTrials.gov under registration number NCT05125146.

**Fig 1 pone.0285757.g001:**
[figure not shown]
Standard Protocol Items: Recommendations for Interventional Trials (SPIRIT) schedule of enrollment, interventions, and assessments. Note: T = Timepoint; T1 and T2 = Baseline; T3 = Intervention; T4 = post 7-week intervention. ISI = Insomnia Severity Index; TIB = Time in Bed; SE = Sleep Efficiency; SOL = Sleep Onset Latency; WASO = Wake Time after Sleep Onset; NOW = Number of Nocturnal Awakenings; TST = Total Sleep Time; SQ = Sleep Quality. Adherence/Engagement = the number of logins; the number of homework and questionnaires completed; the number treatment sessions completed; compliance to keeping a consistent sleep schedule, avoiding naps, eliminating consuming alcohol or nicotine 2–3 hours before going to bed, getting out of bed shortly after waking and completing thought examination practices * = assessments for the e-CBTi group only.

**Fig 2 pone.0285757.g002:**
[figure not shown]
Participant flow chart.

### Sample size

A priori power analyses using the G*Power V3.1 software indicated that a sample size of 36 participants would provide adequate power to detect a medium (f = 0.25) group x time interaction effect using repeated measures analysis of variance (ANOVA) with four sequential measurements per subject per week when the correlation among the measures was 0.3 (α = 0.05). Given the likelihood of participant dropout or withdrawal, participants have been purposely over-sampled to obtain meaningful and statistically significant results regarding changes in their symptoms at the end of the study. Based on previous experience with e-CBTi in similar patient populations, a dropout of up to 25% is anticipated [38]. Considering that former studies of similar nature have suggested that N = 20, 30, 24 per study arm has produced statistically significant interaction effects [39–41]. A sample size of 30 participants in each arm or 60 participants in total, is planned to be recruited for this study to detect significant results with p = 0.05 after expected attrition.

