### Outcome evaluation

All participants are expected to wear the Fitbit sleep tracking device during the study duration and complete the Insomnia Severity Index (ISI) questionnaire and sleep diary on the OPTT platform at baseline (week 0), weekly during the study, and post-treatment (week 7–8). A tutorial for using the sleep diary on the platform will be provided to all participants. An independent researcher will collect all quantitative and qualitative measures by extrapolating recorded information through the OPTT platform.

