### Statistical analyses

SPSS version 25 will be used to analyze the data (e.g., analyses of missing values, baseline characteristics, the effect of the intervention, compliance rates). For all analyses, the alpha level will be set to 0.05. Initially, all data will be examined for missing, nonsensical, and outlying variables. Missing data will be treated as missing and not imputed. Participants who did not complete all seven sessions of e-CBTi or trazodone are considered dropouts. Additionally, dropout rates between groups will be compared using chi-square tests, and demographic and dependent variables will be assessed and compared between completers and participants who withdraw prematurely to estimate dropout effects. Descriptive statistics will be used to describe the sample’s baseline demographics. Group differences in baseline demographics will be analyzed using independent sample t-tests for continuous variables (e.g., age, income). Chi-square test will be used to examine group differences in categorical variables (e.g., sex, ethnicity, native language, employment status, children, current medications, education level, medication usage, living arrangements, and primary diagnosis). Data from all participants will be included in the analyses. Treatment effectiveness will be assessed using two-way ANOVA for repeated measures and multilevel regression analysis with the main effects as the group (e-CBTi vs trazodone) and time (pre-treatment to post-treatment). The group x time interaction effects for the ISI scores, sleep diary measures, and Fitbit sleep estimates will be evaluated to compare the change from pre-treatment to post-treatment between and within the groups. Descriptive statistics will be used to describe the sample and patient engagement, including the number of logins, the number of sessions completed, and the number of homework or questionnaires submitted. An independent sample t-test will be used to identify group differences regarding these behavioural variables.

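### The sample-size calculation assumes four measurements per week, which is not how the primary ISI comparison is measured or tested, so its power statement should be redone for the pre-to-post contrast.

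*Protocol article*

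**What the plan says.** Under Sample size, the article states that "a sample size of 36 participants would provide adequate power to detect a medium (f = 0.25) group x time interaction effect". The inputs are a G*Power calculation "using repeated measures analysis of variance (ANOVA) with four sequential measurements per subject per week when the correlation among the measures was 0.3" and a significance level of 0.05. No target power is given beyond the word adequate. The same section anticipates up to 25% dropout, notes that in earlier trials "N = 20, 30, 24 per study arm has produced statistically significant interaction effects", and sets recruitment at 60, or 30 per arm.

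Under Primary outcome, the outcome is the ISI. Under Outcome evaluation, it is completed "at baseline (week 0), weekly during the study, and post-treatment (week 7–8". Under Statistical analyses, the factors are group and "time (pre-treatment to post-treatment", for both a two-way repeated-measures ANOVA and a multilevel regression. Under Secondary outcomes, the sleep diary is to be filled in on at least four days each week.

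**The concern.** The number of repeated measures is a direct input to this type of power calculation: at a fixed f and correlation, more measures give more power. The article enters four and describes them as four per week. Nothing about the ISI fits that. It is collected once a week, and the comparison as worded has two levels of time. The only outcome with a figure of four per week is the sleep diary, which is secondary, and nights within a week are not the time factor in any stated analysis.

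Two things are at stake. The statement that 36 participants suffice may not hold for the comparison the trial will make. And because neither a target power nor a difference in ISI points is given, a reader cannot tell how large a gap between e-CBTi and trazodone the trial is able to detect.

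**Working it through.** **Inputs.** From Sample size: f = 0.25, correlation r = 0.3, alpha = 0.05, N = 36, dropout up to 25%, recruitment 60. From the design: two groups, 1:1. Expected completers: 60 x 0.75 = 45.

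**Formula** (repeated-measures ANOVA, within-between interaction, two groups, m measures, sphericity assumed): noncentrality lambda = f² x N x m / (1 - r), with df1 = m - 1 and df2 = (N - 2)(m - 1). Power is the probability that a noncentral F exceeds the 5% critical value.

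**Step 1: reproduce the plan's figure (m = 4).** lambda = 0.0625 x 36 x 4 / 0.7 = 12.86, df 3 and 102, power 85.2%. The smallest even N is 32 for 80% power, 36 for 85% and 42 for 90%. So 36 is right for the design entered, with an implied target of 85%.

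**Step 2: the contrast as worded (m = 2, pre and post), same f and r.**

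| N | lambda | df | Power |
|---|---|---|---|
| 36 | 0.0625 x 36 x 2 / 0.7 = 6.43 | 1, 34 | 69.3% |
| 45 | 0.0625 x 45 x 2 / 0.7 = 8.04 | 1, 43 | 79.1% |
| 46 | 0.0625 x 46 x 2 / 0.7 = 8.21 | 1, 44 | 80.0% |
| 60 | 0.0625 x 60 x 2 / 0.7 = 10.71 | 1, 58 | 89.6% |

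**Step 3: what f = 0.25 means here.** In a 2 x 2 layout each of the four cells carries an interaction effect of +e or -e, and f = e / SD. The between-arm difference in change is the sum of the four, 4e = 4f x SD = 1.0 SD of a single score. The SD of a change score is sqrt(2 x (1 - 0.3)) = 1.18 SD, so the same difference is 1 / 1.18 = 0.85 SD of change.

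**Step 4: check by the change-score t-test.** At N = 36 the noncentrality is 1 / (1.183 x sqrt(4/36)) = 2.54, and 2.54² is about 6.43, the lambda of Step 2.

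**Step 5: detectable difference.** At 80% power and r = 0.3, it is about 1.14 SD with 36 participants, 1.01 SD with 45 and 0.87 SD with 60.

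**The case against.** The strongest reply is that the trial does not stop at 36. It recruits 60, and at the plan's own effect size the 45 expected completers are one short of the 46 needed for 80%. That stands, and it limits the practical consequence. It does not make the sentence about 36 correct.

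A second reply is that weekly ISI scores exist and a multilevel regression is planned alongside the ANOVA. With 8 or 9 measures, nominal power at f = 0.25 and N = 36 would be 97 to 98%. That reading is open for the multilevel model, but it is neither four per week nor the pre-to-post effect that the analysis section names.

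Third, the four might be the timepoints T1 to T4 in the Fig 1 note, with a stray reference to the week. That is possible, but two of those four are baseline, so they do not match the tested contrast either.

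Fourth, r = 0.3 may be cautious. At an assumed r = 0.5 the two-point power is 83% at 36 and 91% at 45. The article itself chose 0.3.

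Some stronger inferences are tempting but unsupported:

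- **That 36 is miscalculated.** It reproduces for its inputs.
- **That medium is a mistake.** f = 0.25 is the conventional label; the trouble is only that it goes untranslated.
- **That the trial is underpowered for a half-SD difference.** Power for that would be about 28% at 45 completers, but the article never claims that target.
- **That the step from 36 to 60 is an error.** The article does not present 60 as 36 inflated for dropout. That inflation would give 36 / 0.75 = 48, and 60 exceeds it.
- **That a null result would be reported as equivalence.** The stated hypothesis is superiority, and no equivalence conclusion is planned.

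**Conclusion.** The power calculation describes a measurement pattern that the primary outcome does not have. For the pre-to-post ISI comparison, at the plan's own f and r, 36 participants give about 69% power, against the 85% implied by the design entered, so the claim of adequate power at 36 is not supported as written. At the numbers the trial plans to have, power is about 79% with 45 completers and 90% if all 60 contribute, for a difference in change of 1.0 SD of a single score.

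These figures assume two time points, r = 0.3, two arms of nearly equal size and 45 evaluable participants. The last is not certain: dropout is defined by incomplete treatment and all participants' data are to be analysed, so some dropouts may still supply an ISI score. The statement should be corrected, but the point does not call the sample size of 60 into question.

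**What to change.** Keep 60. In the Sample size section:

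1. Replace the phrase about four measurements per week with the number of ISI time points that the primary analysis uses, and make it agree with Statistical analyses.
2. State the target power and restate the result for that contrast. For pre to post: about 79 to 80% power for a 1.0 SD difference in change, with 45 completers, r = 0.3 and two-sided alpha 0.05.
3. Translate f = 0.25 into a difference in ISI points under a stated SD, so that medium is not left to stand alone. The article gives no ISI SD, so the investigators must supply one.

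If the weekly scores are meant to carry the primary test, say so and compute power for that model instead.

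The cost is rewording. No participants are added. The stated power at 36 becomes less favourable, and the size of the detectable difference becomes visible to readers.
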